#### Sampling strategies

For the case study, we will use a purposive sampling strategy to represent the macro, meso, and micro levels of care: namely, healthcare professionals, decision makers within the organization (CSSS-VC), and decision makers within regional health boards. Participants will be recruited from the following categories: (i) patients receiving home care (n = 5-8) and their caregivers (n = 5-8); (ii) administrators such as managers and policy makers who have varying influence on the home care environment (n = 4-6); and (iii) professionals from IP teams who have a significant impact on healthcare decisions (n = 5-8). Eligible healthcare professionals will include physicians, nurses, dieticians, social workers, rehabilitation therapists, respiratory therapists, pharmacists, and psychologists. Eligible patients will consist of adults with family caregivers.

For the survey, we will contact the approximately 300 healthcare professionals who provide home care for patients affiliated with one of the CSSS-VC's three sites. These patients hail from the CSSS-VC's four main groups of home care patients: patients recovering from hospitalisation, older people, end-of-life patients, and patients with mental health problems.

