For the survey, we will send a questionnaire based on the Theory of Planned Behaviour (TPB) to all healthcare professionals. This information will allow us to measure professionals' intentions to engage in an IP approach to SDM in home care and adapt our framework for the assessment of barriers to the implementation of SDM [16]. The TPB posits that intention is the immediate determinant of changes in behaviour [33]. It suggests that for a behaviour to change, salient beliefs underlying the factors found to be significantly associated with behavioural intention(e.g., attitude, social norms, perceived behavioural control) should be reinforced by a theory-based intervention. The TPB survey will solicit the information necessary to create interventions that increase the uptake of the desired behaviour. Our survey questionnaire will be based on validated questionnaires developed by our research team for similar projects on the implementation of SDM in clinical practice [16,34,35].

In addition to conducting a case study and a survey, we will review documents throughout the study to determine how the context at the meso and macro levels influences an IP approach to SDM at the micro level. For this, we will consult the CSSS-VC's mission statement, its description of its home care program, and other organizational documents such as newsletters, clinical protocols and regulatory documents. We will seek corroboration in exemplars discussed in the individual interviews or the focus group.

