#### Phase 3: Appraising the toolkit

After developing the toolkit, we will once again work with the case study participants of phase 1 (administrators, patients, caregivers, and healthcare professionals) to (i) obtain feedback on the revised IP SDM model, (ii) reassess providers' intention to adopt an IP approach to SDM in home care, and (iii) appraise the feasibility and acceptability of the new toolkit of interventions to implement an IP approach to SDM in professionals' practice of home care. We will administer an acceptability and feasibility questionnaire using tools validated with other SDM programs [37,38]. This questionnaire will ask users to rate the amount of information supplied with each intervention, the clarity of the information in question, and the overall presentation of the intervention. It will also ask users to identify any factors that could influence implementation of the intervention.

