#### Survey

In the secondary objective, we will numerically code respondents' intention to engage in an IP approach to SDM, the determinants of their intention, their acceptance of the toolkit interventions, and their sociodemographic data. All data will be entered into an Excel file. We will conduct descriptive analyses of the survey items using Excel software so as to fulfill objectives 2 and 3. We will explore differences in responses to the TPB surveys in phases 1 and 3 regarding respondents' intention to engage in an IP approach to SDM.

In a pilot clustered randomized control trial of a SDM training program, the intention of family physicians to engage in SDM was 0.8 (possible range -3 to +3) at baseline [40]. We assume that the minimal clinically significant difference in the intention of health professionals to engage in an IP approach to SDM between the phases 1 and 3 is 0.2. In order to detect an increase from 0.8 to 1.0 in the intention of health professionals to engage in an IP approach to SDM with 80% power, at a 5% significance level, one would require 126 health professionals in the study. However, it is important to consider that this present study involved health professionals from various disciplines.

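### The 80% power stated for the phase 1 to phase 3 change in intention rests on 126 professionals, but phase 3 as described re-measures only the 5–8 in the case study

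*Protocol article*

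**What the plan says.** The Survey section (under Data analysis) announces the comparison: "We will explore differences in responses to the TPB surveys in phases 1 and 3". It takes 0.2 points, on a scale from -3 to +3, as the minimal clinically significant difference between those two phases. It then sizes the comparison: "In order to detect an increase from 0.8 to 1.0 in the intention of health professionals", with 80% power and "at a 5% significance level", "one would require 126 health professionals in the study". The only caveat that follows is that several disciplines are involved.

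Three other places say who is measured:

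- **Phase 1, survey.** Sampling strategies: "we will contact the approximately 300 healthcare professionals who provide home care". The Phase 1 section agrees: "we will send a questionnaire based on the Theory of Planned Behaviour (TPB) to all healthcare professionals".
- **Phase 3.** "we will once again work with the case study participants of phase 1". Reassessing providers' intention is listed as part of that work.
- **Case-study size.** Sampling strategies recruits "professionals from IP teams who have a significant impact on healthcare decisions (n = 5-8"). The other participants are patients (5–8), caregivers (5–8) and administrators (4–6).

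**The concern.** The sample size serves a before-and-after comparison, so it must count people who have a value at both phases or, if the phases are compared unpaired, enough people at phase 3. The large survey is described for phase 1 only. The one description of who takes part in phase 3 leads back to the case study, where at most 8 people are health professionals. Patients, caregivers and administrators are not the population of the calculation. The Alberta team of about 20 belongs to phase 4 and adds no phase 3 data.

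This is the only power statement in the article. A reader could take it to mean that the study is able to see a 0.2-point shift, and could then give a flat phase 3 result more weight than it can carry.

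**Working it through.** **Inputs from the article.** Difference 0.2 (0.8 to 1.0); power 80%; significance level 5%; required number 126; phase 1 survey about 300; case-study professionals 5–8.

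**Inputs not given.** SD, one- or two-sided test, paired or unpaired comparison. Each is treated below as an assumption.

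**Step 1: reproduce 126.** For a paired comparison, n = [SD × (z_α + z_power) / 0.2]².

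- Two-sided, SD of change 0.80: [0.80 × (1.960 + 0.842) / 0.2]² = 125.6, rounded up to 126.
- One-sided, SD of change 0.90: 125.2, rounded up to 126.
- Unpaired, two-sided: SD about 0.57 gives 126 per phase; SD about 0.40 gives 63 per phase.

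So 126 is a plausible figure, but the article does not settle which calculation produced it.

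**Step 2: power with 5–8 professionals, two-sided paired.** On this reading 126 and 80% power fix the standardised change at (1.960 + 0.842) / √126 = 0.25, so no separate SD is needed. Noncentral t power at the two-sided 5% level:

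| n | Power |
|---|---|
| 5 | 7.2% |
| 6 | 8.0% |
| 7 | 8.7% |
| 8 | 9.4% |
| 126 | 79.5% |

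The last row checks the method: it returns the planned 80%, apart from the small loss from using t in place of the normal.

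**Step 3: vary the assumptions (5 to 8 professionals at phase 3).**

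| Assumption | Power |
|---|---|
| Paired, two-sided, SD of change 0.5 to 1.2 | 6% to 17% |
| Paired, one-sided, SD of change 0.90 | 11% to 14% |
| Unpaired, two-sided, 300 v 5–8, SD 0.80 | 9% to 11% |
| Unpaired, two-sided, 300 v 5–8, SD 0.57 | 12% to 17% |
| Unpaired, two-sided, 300 v 5–8, SD 0.40 | 20% to 28% |

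These run from about 6% to 28%. Combining the two most favourable choices goes a little higher. For an unpaired, one-sided test with the SD that fits 63 per phase (0.2 × √(63/2) / 2.486 = 0.45) and 300 v 8, the noncentrality is 0.2 / [0.45 × √(1/300 + 1/8)] = 1.24. Power is then about Φ(1.24 − 1.645) = 34%.

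**Step 4: what 5–8 pairs can show, if the SD of change is 0.80.**

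- 95% CI half-width, t × 0.80 / √n: 2.776 × 0.80 / √5 = 0.99 for n = 5; 2.365 × 0.80 / √8 = 0.67 for n = 8.
- Change detectable with 80% power: 1.35 points (n = 5) to 0.92 points (n = 8), against the planned 0.2.

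**Step 5: could other participants make up the number?** Counting every case-study participant gives 5+5+4+5 = 19 to 8+8+6+8 = 30. At a standardised change of 0.25, power is 18% to 26%, and most of these people are not health professionals.

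**The case against.** The best defence is that a repeat survey of all staff was intended. The Survey section speaks of TPB surveys in both phases without saying who answers the second. It also lists acceptance of the toolkit among the data to be coded. The Phase 3 section does not name the TPB instrument, and a journal article may shorten survey logistics. On that reading 126 of about 300 (126/300 = 42%) might be reachable. This part stands: it would be too strong to infer that 126 can never be reached. What the text supports is that the sections disagree about who is re-measured. It does not rescue the power statement, because the only passage that names the phase 3 participants limits them to the case study.

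A second defence is that the comparison belongs to the secondary objective, is described as exploratory, has descriptive analyses and names no test, and that the case study is the main component. This also stands, and it lowers the consequence. A reader might infer that a null result will be reported as no change at 80% power, but the article plans no such inference. Even so, the section attaches a minimal important difference, a significance level and a power to this comparison, and nowhere says that the number will not be met.

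A reader might also infer that 126 is miscalculated, or that power is 7–9% without conditions. Neither is supported. The figure 126 follows from plausible inputs, and 7–9% depends on a two-sided paired test that the article does not state.

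**Conclusion.** The point holds as an internal inconsistency between the Survey, Phase 3 and Sampling strategies sections. As described, at most 8 health professionals have a phase 3 value, against the 126 said to be required, and the stated 80% power does not apply. The size of the shortfall is conditional on the unstated SD, sidedness and pairing, but the conclusion is not: even the most favourable combination tried stays below half of the stated power. Severity is moderate, since the comparison is secondary and exploratory.

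**What to change.** **If phase 3 stays with the case study.** In the Survey section, withdraw the 80% power statement for the phase 1 v phase 3 comparison. State that intention is re-measured in the 5–8 case-study professionals. Report each individual change and the mean change with a 95% CI (expected half-width about 0.7–1.0 points if the SD of change is 0.80). Make no test against 0.2, and draw no conclusion of no change from a null result. The cost is wording and a less favourable statement of power.

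**If a repeat TPB survey of the roughly 300 was intended.** Amend the Phase 3 section to say so, set 126 linked pairs (about 42%) as the target, and state the SD and the test behind 126. This costs more than a mailing. The toolkit is developed in phase 2 and appraised by the case-study participants, so the wider staff would also need exposure to it.

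The 126 should not be reused as a precision target for the phase 1 survey. The back-solved 0.80 is an SD of change, and it equals the SD of a single measurement only if variances are equal and the correlation between phases is 0.5, which the article does not say.

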#### Mixed methods: integration of qualitative and quantitative data

We will use NVivo to triangulate quantitative and qualitative findings from the different sources. To comply with rigorous methodological strategies [41], the two co-principal investigators, the co-investigators, and the research assistants associated with the home care setting will review the case study. This will generate feedback regarding the credibility of our model in the home care setting.

#### Organizational documents

Research assistants will perform content analysis of organizational documents under the leadership of a co-principal investigator. The content analysis will use a similar approach to that used to analyze the transcripts. The documents in question are expected to be a particularly important source of information, allowing us to reach our research objectives 1 and 2. We will use the notes and findings from the documents to better understand the organizational context, variations and deficiencies in current practices, and respondents' perceptions of the factors influencing an IP approach to SDM in home care.

### Ethical considerations

This research protocol was reviewed and approved by the CSSS-VC Research Ethics Board. All participants will sign consent forms approved by the CSSS-VC Research Ethics Board.

## Discussion

### Expected outcomes

To respect Canadian health policies that emphasize the need for an IP approach to patient-centered care, [42,43] it is necessary to develop tools to implement IP SDM practices in home care settings. Our IP SDM model and the support of well-trained IP healthcare teams can help home care patients become better informed, help them better understand their own health outcomes, and help them make health decisions that respect their values and preferences. This study will generate practical, policy-oriented knowledge of interventions to broaden the implementation of IP SDM in home care.

### Potential limits of the proposed research

One limitation of the proposed study is that we will only present one case. Nonetheless, our experience developing our initial IP SDM model persuades us that it is important that we advance systematically to ensure that we address barriers successfully and adapt the IP SDM model iteratively. Future work will build on the solid evidence obtained from this study and will involve multiple sites, and hence more cases, so as to ascertain the transferability of our approach across settings. The pilot project in Alberta will be an important first step in this process.

### Knowledge translation plan

This study will deliberately employ an integrated knowledge translation approach. Knowledge users will be integral members of our research team and will provide direct feedback on our new model and interventions, ensuring that these are relevant to the home care setting. The intended users of our results are healthcare teams, educators, and health policy makers interested in implementing patient-centered care processes such as an IP approach to SDM in clinical practice. We expect that many of our collaborators will use our model in the future. In addition to practicing integrated knowledge translation with our participants, at the end of our grant period, we will disseminate study results at scientific and professional conferences whose themes relate to SDM, IP, and health policy. We will also post our results on the websites of our team members' institutions of affiliation and publish our findings in open-access journals. We will disseminate key findings and the toolkit using Canadian web-based dissemination vehicles that address home care issues.
